### Oesophageal Doppler

An oral oesophageal Doppler probe (Deltex Medical, Chichester, UK) will be inserted at the same time as acquisition of the first IDF images. The probe will remain in situ continuously for 72 h or until the patient is ready for extubation. The following data will be recorded: corrected flow time, stroke volume, cardiac output. Data obtained from this monitoring device will also be available for use to the patients’ attending clinicians if they wish.

### Thromboelastography (ROTEM)

A 5 ml sample of blood will be withdrawn from existing vascular access devices and used to perform point-of-care analysis of coagulation status using the technique of thromboelastography (ROTEM). The following values will be recorded: EXTEM/FIBTEM CFT, A5, A10, MCF, LY 30.

### Biological sampling

Samples of blood and urine will be withdrawn from existing vascular access devices and stored for later assessment of the mechanisms of microcirculatory dysfunction.

### Physiological and pharmacological data

The following parameters will also be recorded at every time point where available:
SBP, diastolic blood pressure and mean arterial blood pressure;Central venous pressure;Heart rate;Arterial Blood Gas Data (including lactate, base deficit, arterial oxygen saturation, arterial carbon dioxide saturation)Haemoglobin concentration;Central Venous Blood Gas Data (central venous oxygen saturation (ScvO_2_), central venous carbon dioxide saturation (ScvCO_2_));Plasma (free) haemoglobin;Administration of blood, blood products and bolus challenges of other intravenous fluids since the previous time point;Type of sedative drug infusions currently being administered;Type and dose of inotropic and vasopressor drugs currently being administered.

### Primary outcome

The primary outcome is the Sequential Organ Failure Assessment (SOFA) score at the D3 time point (72 h after admission to ICU), and will be recorded using information from the patients’ charts and laboratory results.

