## Background

Massive haemorrhage and associated shock is a leading cause of preventable death among casualties with severe traumatic injury, accounting for around 40–50% of all deaths.^1^
^2^ Despite significant improvements in treatment and mortality within this patient group, systemic inflammatory response, coagulopathy and subsequent multiple organ failure remain common.^3^ These issues can lead to prolonged periods of morbidity, critical care dependency and often death. Therapeutic interventions that attenuate these responses may lead to significant benefit for patients who have suffered traumatic haemorrhagic shock (THS).^3^

The microcirculation is of particular clinical importance during circulatory shock since it is this network of capillaries and other small vessels that perform the essential functions of delivering oxygen and substrates to cells. Traditionally, resuscitative strategies are guided by measurement of global haemodynamic parameters such as blood pressure and cardiac output. However, there may be a poor correlation between such global parameters and the appearance of the microcirculation.^4^
^5^ Microcirculatory parameters may also predict outcome better than more conventional global circulatory measurements in sepsis.^6^ Observational data suggest patients who can improve the state of the microcirculation in response to resuscitative fluid therapy have a better outcome than those who cannot.^7^
^8^

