### Primary objective

The primary objective of the MICROSHOCK study is to examine the microcirculatory function in patients following THS, and to determine whether these parameters are superior to global haemodynamic parameters in the prediction of clinical outcomes.

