### Analysis of IDF video sequences

Prior to analysis, the recorded video sequences will be edited into at least three (and no more than five) video clips. All clips will be rated for quality using a five-point scale.^17^ Substandard images will be rejected. All IDF images will be analysed using a dedicated software tool (Automated Vascular Analysis V.3.02, Microvision Medical, The Netherlands). This is a semiautomated process which produces a number of data points from the video sequence. Analysis of the video clips will produce the following data:
Microvascular flow index;Total vessel density;Perfused vessel density;Proportion of perfused vesselsMicrocirculatory heterogeneity index.

This process is in accordance with recommendations made by an international consensus conference on assessing the microcirculation.^10^ Interobserver variation will be tested at regular intervals in order to minimise heterogeneity of data analysis between investigators. At the time of analysis, the investigators will be blinded with respect to the clinical time point of the study, the patients’ details, and the other outcome variables (SOFA score and haemodynamic data).

The following relationships will be examined:
Between microcirculatory parameters during the postresuscitation period and the development of SOFA scores;Between microcirculatory parameters and systemic haemodynamic data (stroke volume, cardiac output, blood pressure);Between microcirculatory parameters and plasma lactate and ScvO_2_ over the resuscitation period;Between microcirculatory parameters and coagulation parameters as assessed by ROTEM.

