### Statistical analysis

Normally distributed data will be presented as mean and SD, and non-normally distributed data will be presented as median and IQR. For comparison, patients will be dichotomised according to day 3 SOFA score into those with a score ≥6 versus those with SOFA score <6. The score of 6 has been chosen due to its prognostic relevance^18^ and previous utilisation as an end point for haemorrhagic trauma patients.^16^ Further analysis will be conducted according to the change in SOFA scores between days 1 and 3, so that patients are dichotomised into SOFA score ‘improvers’ and ‘non-improvers’. This approach has also been used as an end point for haemorrhagic trauma patients.^19^ Groups will be compared using a two-tailed t test for normally distributed data and the Mann-Whitney U test for non-normally distributed data. A p value of <0.05 will be considered statistically significant.

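### Blood pressure is both a competing predictor and, through the cardiovascular item, part of the day 3 SOFA score used to judge the competition

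*Protocol article*

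**What the plan says.** - **Question.** Protocol article, Primary objective: the aim is to examine microcirculatory function and "to determine whether these parameters are superior to global haemodynamic parameters in the prediction of clinical outcomes".
- **Comparators.** The Background gives as examples "global haemodynamic parameters such as blood pressure and cardiac output". Analysis of IDF video sequences lists the relationship "Between microcirculatory parameters and systemic haemodynamic data (stroke volume, cardiac output, blood pressure").
- **Yardstick.** Primary outcome: "The primary outcome is the Sequential Organ Failure Assessment (SOFA) score at the D3 time point", which is 72 h after ICU admission. The score "will be recorded using information from the patients’ charts and laboratory results". No item is set aside.
- **Analysis.** Statistical analysis: "patients will be dichotomised according to day 3 SOFA score into those with a score ≥6 versus those with SOFA score <6". A further split, into SOFA improvers and non-improvers between days 1 and 3, uses the same total score.
- **Data collected.** Physiological and pharmacological data: systolic, diastolic and mean pressure at each time point where available, together with "Type and dose of inotropic and vasopressor drugs currently being administered".
- **Outcomes with no blood pressure content.** Secondary outcomes include 28-day mortality, length of stay and days of ventilation.

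The article does not list the SOFA items.

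**The concern.** When predictors are ranked against an outcome, none of them should be part of how that outcome is scored. Under the standard score, the cardiovascular item is read from mean arterial pressure and vasopressor dose. A patient whose low pressure persists to 72 h therefore scores points for that pressure, whether or not any other organ has failed. Blood pressure gains predictive credit from its own persistence, and no microcirculatory index has a matching item.

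The shift works against the study's hypothesis. What is at stake is a real microcirculatory advantage that goes unseen, or an apparent blood pressure effect that is partly overlap. Both matter because the results are meant to shape later goal-directed interventions.

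**Working it through.** The plan gives no AUC, effect size or power for this comparison, so there is no figure of its own to reproduce. The check asks which way the overlap pushes, and how far.

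**Inputs from the protocol:** total SOFA at D3, cut at 6; N = 60; Mann-Whitney test at p < 0.05; blood pressure among the comparators.

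**Assumptions:** the standard score with six items of 0 to 4 points, one of them cardiovascular; the distribution of that item; the distribution of the other five items; and the correlation between early blood pressure and the D3 cardiovascular state (the carry-over).

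**Step 1: what one item can do at the cut.** With a cardiovascular score of 0, a patient needs 6 points from the other five items to reach the upper group. With a score of 4, the same patient needs 6 − 4 = 2.

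**Step 2: neither marker predicts other-organ failure.** The cardiovascular item takes the values 0/1/3/4 from a latent normal state. The other items sum to a mean of about 4 (SD 2.5), set higher in the lighter case so that about half of patients still reach 6. Blood pressure = ρ × latent cardiovascular state + √(1 − ρ²) × noise, and the microcirculatory marker is pure noise. AUCs come from 400,000 simulated patients and significance rates from 4,000 studies of 60. Where repeated runs differed, the range is shown.

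| Cardiovascular item 0/1/3/4 | ρ | AUC, blood pressure | Studies with p < 0.05 |
|---|---|---|---|
| 40/25/20/15% (35% at 3 or 4) | 0.3 | 0.57 | 13–15% |
| | 0.5 | 0.61 | 31–33% |
| | 0.7 | 0.66 | 56–58% |
| 65/25/7/3% (10% at 3 or 4) | 0.1 | 0.51 | about 5–6% |
| | 0.3 | 0.54 | 7–8% |
| | 0.5 | 0.56 | 12–14% |
| | 0.7 | 0.59 | 21–22% |

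The microcirculatory marker stays at AUC 0.50 and about 5% throughout. At ρ = 0, blood pressure does too.

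**Step 3: both markers truly predict, equally well.** In a second model, each marker correlates 0.5 with latent severity, and all six items depend on severity. The cardiovascular item has cut points 0, 0.5, 0.9 and 1.4 on a standard normal scale, so 1 − Φ(0.9) = 18% of patients score 3 or 4. Here ρ is the carry-over beyond shared severity. Without the cardiovascular item both AUCs are 0.70. With it, AUC (blood pressure) minus AUC (microcirculatory) is:

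| ρ | Blood pressure as is | Blood pressure already normalised by treatment |
|---|---|---|
| item left out | 0.00 | −0.07 |
| 0 | 0.00 | −0.06 |
| 0.3 | +0.03 | −0.04 |
| 0.6 | +0.06 | −0.02 |
| 0.8 | +0.08 | −0.02 |

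In the right-hand column the microcirculatory marker still wins, but its lead shrinks.

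**Step 4: set against precision.** The Hanley-McNeil variance is [A(1−A) + (n₁−1)(Q₁−A²) + (n₀−1)(Q₂−A²)] / (n₁n₀), with Q₁ = A/(2−A) and Q₂ = 2A²/(1+A). For A = 0.70, Q₁ = 0.538 and Q₂ = 0.576.
- With 30 and 30 patients: (0.21 + 29 × 0.0485 + 29 × 0.0865)/900 = 0.00458, so SE = 0.068.
- With 18 and 42 patients: (0.21 + 17 × 0.0485 + 41 × 0.0865)/756 = 0.00606, so SE = 0.078.

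The shifts in Step 3 are thus at most about one standard error of a single AUC.

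**The case against.** A reader might infer that the whole comparison is biased by construction against microcirculatory parameters, and that a null or reversed result could not be interpreted. The documents do not support that, for these reasons:

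- **Scope.** Stroke volume and cardiac output, the measures for which Doppler and echocardiography are used, are not items of the standard score. The direct overlap is with blood pressure, and with vasopressor dose only if that were used as a predictor, which the article does not propose.
- **Carry-over.** Readings on arrival or at ICU admission come 72 h or more before the outcome. The article gives no carry-over, and at zero the shift vanishes. Treatment can restore the measured pressure, in which case blood pressure may predict worse than the microcirculatory marker even with the item included.
- **Vasopressor use.** The Discussion describes high vasopressor use as relatively uncommon in the UK, and all sites are in the UK. An assumption of 35% at item score 3 or 4 therefore looks high.
- **Other outcomes.** Mortality, length of stay and ventilation days contain no blood pressure item and can be set beside the SOFA result.
- **Meaning.** Cardiovascular failure is itself organ failure, so predicting it is not purely artefact. The shift also runs against the hypothesis and cannot create a false claim of microcirculatory superiority.
- **Place.** An extra analysis of this kind may sit in a full protocol or analysis plan that is not shown.

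The first five points stand and limit the concern. The last stands only in part: the overlap follows from choices the article itself fixes (total score, cut-off and comparators). If the unseen plan already has such an analysis, nothing more is needed.

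**Conclusion.** The point holds for blood pressure. It is one of the competitors in the primary question and, under the standard score, part of one item in six of the primary outcome. Any carry-over of early blood pressure to D3 moves the comparison in its favour and can hide a microcirculatory advantage.

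The size is uncertain and depends entirely on assumptions. Where neither marker predicts other-organ failure, the blood pressure AUC lies between about 0.51 and 0.66 rather than at 0.50, with roughly 6% to 58% of 60-patient studies significant, for carry-over of 0.1 to 0.7 and 10% to 35% of patients at item score 3 or 4. The lighter distribution fits the Discussion better and gives the lower part of that range. Where both markers predict equally, the second model gives a shift of 0 to 0.08 in AUC. The effect shrinks under milder assumptions but disappears only without carry-over. Total SOFA remains a reasonable primary outcome; what is needed is a second look that separates overlap from prediction.

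**What to change.** - Keep total D3 SOFA as the primary outcome.
- Pre-specify that the comparison of microcirculatory parameters with blood pressure is repeated on D3 SOFA without its cardiovascular item. Analyse this as a score, because the cut at 6 belongs to the full total.
- Report blood pressure separately from stroke volume and cardiac output, so that the overlap is not attributed to the flow measures.
- State that a blood pressure advantage, or a null result, will be interpreted in the light of both analyses.

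The cost is one extra analysis on a reduced score that readers will know less well. The item scores are needed to form the total anyway, so no new data are required.

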### Exclusion criteria

Patients with facial injuries, where access to the sublingual area would be problematic will be excluded. Patients with injuries deemed unsurvivable in whom the focus of care is palliation rather than active treatment are also ineligible for inclusion.

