**Figure 1 BMJOPEN2015010893F1:**
[figure not shown]
Sampling and techniques. BP, blood pressure; ED, emergency department; GCS, Glasgow Comas Scale; ICU, intensive care unit; IDF, incident dark field; HR, heart rate; RR, respiratory rate.

Where feasible, and appropriate, further readings will be taken between the first and second time points. Data collection is stopped once the patient has been extubated.

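### Total SOFA at 72 h, cut at 6, lets the consciousness item supply up to 4 of the 6 points in intubated patients with brain injury not excluded; a five-item SOFA should be prespecified beside it

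*Protocol article*

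**What the plan says.** All references are to the protocol article.

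- **Primary outcome.** The outcome is the "Sequential Organ Failure Assessment (SOFA) score at the D3 time point (72 h after admission to ICU"), and it "will be recorded using information from the patients’ charts and laboratory results". No item is left out of the score.
- **Statistical analysis.** For the group comparison, "patients will be dichotomised according to day 3 SOFA score into those with a score ≥6 versus those with SOFA score <6". The cut is justified by its prognostic relevance and by earlier use in haemorrhagic trauma. A second analysis uses the same score: "Further analysis will be conducted according to the change in SOFA scores between days 1 and 3".
- **Inclusion criteria.** Intubation and ventilation are required, together with a raised lactate, a mechanism consistent with blood loss, and blood products received or predicted.
- **Exclusion criteria.** There are two. The first is "Patients with facial injuries, where access to the sublingual area would be problematic will be excluded"; the second is unsurvivable injury under palliative care. Survivable brain injury is therefore eligible.
- **Physiological and pharmacological data.** Among the items recorded at each time point, where available, is "Type of sedative drug infusions currently being administered".
- **Time points and techniques for data collection.** "Data collection is stopped once the patient has been extubated".
- **Primary objective.** The study asks whether microcirculatory parameters predict clinical outcome better than global haemodynamic parameters.

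**The concern.** The study wants an outcome that reflects organ failure following haemorrhagic shock. One of the six SOFA items is the level of consciousness. In this population that item has two plain sources other than perfusion: drugs given to a ventilated patient, and a direct brain lesion.

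A patient with the maximum on that item needs 2 points from the other five to enter the worse group. A fully conscious patient needs 6. The two groups compared in the main analysis could thus differ partly in sedation or injury pattern. If those points are unrelated to perfusion, true associations are diluted. If they track something that also affects the predictors, associations are confounded. The analysis of change from day 1 to day 3 is exposed in the same way, since a change in sedation alone could move the score by up to 4 points.

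**Working it through.** There is no stated power or effect size to reproduce: the article gives 60 patients without statistical inputs. The check is therefore what the consciousness item can contribute, followed by illustrations on assumed inputs.

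**1. Share of the cut-off.** Input from the article: the cut of 6. Assumption: six items, each 0 to 4, because the article does not print the score. With c points on consciousness, the share of the cut is c/6 and the other five items must supply 6 − c.

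| c | share of 6 | needed from other five items |
|---|---|---|
| 0 | 0% | 6 |
| 1 | 17% | 5 |
| 2 | 33% | 4 |
| 3 | 50% | 3 |
| 4 | 67% | 2 |

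The item supplies more than half of the threshold only at its maximum.

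**2. Does a scoring rule remove the problem?** There are two usual conventions. Observed GCS carries the effect of sedation. An assumed or last pre-sedation GCS removes sedation but keeps head injury, which the exclusion criteria allow. Neither leaves an item that reflects perfusion alone.

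**3. Loss for a continuous score (illustration).** Assume the item is 0 or 4, a proportion p of patients score 4, and the item is independent of the predictors and of the other five items, whose variance is V. The item's variance is 16p(1 − p). The correlation of a predictor with the total is its correlation with the five items multiplied by √(V / (V + 16p(1 − p))). The square of that factor times 60 gives the equivalent number of patients.

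- SD 2.5, p 0.5: √(6.25/10.25) = 0.78; 60 × 0.610 ≈ 37
- SD 3, p 0.5: √(9/13) = 0.83; 60 × 0.692 ≈ 42
- SD 3.5, p 0.3: √(12.25/15.61) = 0.89; 60 × 0.785 ≈ 47
- SD 3, p 0.9: √(9/10.44) = 0.93; 60 × 0.862 ≈ 52
- SD 3.5, p 0.9: √(12.25/13.69) = 0.95; 60 × 0.895 ≈ 54

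The loss is greatest when half the patients are at the maximum and shrinks when nearly all are, because the item is then almost constant.

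**4. Patients moved across the cut (illustration).** Simulation assuming the other five items sum to a Poisson count with mean 4 to 6, and that 30% to 60% of patients independently score 4 on consciousness. Among patients classed as 6 or more, about 19% (mean 6, 30%) to 66% (mean 4, 60%) would be below 6 on the other five items.

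**5. Effect on the planned two-group test (illustration).** With 60 patients split 30/30 and two-sided α 0.05, the standardised difference detectable with 80% power is (1.96 + 0.84) × √(2/30) = 0.72. Suppose a fraction f of the worse group is there only through consciousness points and has predictor values like the better group. The difference becomes 0.72 × (1 − f), and power falls to 71%, 61%, 50% and 29% for f = 10%, 20%, 30% and 50%.

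**The case against.** The strongest reply is that the article is a condensed document. How GCS is scored under sedation is an operational rule that may well stand in the full protocol or the analysis plan. That is right, and the absence of the rule here is not counted as an error. If a pre-sedation value is used, the sedation part falls away; the head-injury part does not.

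Several stronger readings are tempting and are not supported:

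- *Most patients are sedated at 72 h.* The article plans to record the type of sedative infusion. It gives no frequency or depth.
- *All patients are still intubated at 72 h.* Intubation is an entry criterion. Data collection stops at extubation, but a chart-based score could still be taken afterwards.
- *Sedation practice differs between the three centres.* Nothing in the article says so.
- *The study loses a known share of its information.* The figures in step 3 treat the item as 0 or 4 and independent of everything else, and they concern a continuous score rather than the planned split. If sicker patients are sedated for longer, that formula does not apply.
- *The comparison of microcirculatory with global parameters is biased.* The item can disturb both sets of predictors. A bias in favour of either has not been shown.
- *Total SOFA must be replaced as primary outcome.* The article justifies the cut of 6, the consciousness item can also capture genuine cerebral dysfunction, and no cut-off exists here for a five-item score.

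The article also says that differences in injury pattern will be addressed in the analysis. It collects Injury Severity Score and admission GCS, and it lists secondary outcomes that do not use GCS, such as mortality and ventilation days. This helps with head injury in part. It does not show whether an association with total SOFA comes from the consciousness item.

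**Conclusion.** The concern holds as a limited weakness of the outcome. On the assumed item range of 0 to 4, up to 4 of the 6 points that define the worse group can come from an item that, in this population, may reflect sedation or head injury. This follows from what the article fixes: the whole score, the cut at 6, intubation at entry, and no exclusion of survivable brain injury. An unseen scoring rule would change which of the two influences remains, but would not remove both.

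The size of the effect cannot be derived from the documents. The attenuation of 0.78 to 0.95 (SD of the other items 2.5 to 3.5, 30% to 90% of patients at the maximum) and the misclassification and power figures are illustrations. The result is harder to interpret as organ dysfunction after haemorrhage; the study is not invalidated.

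**What to change.** Prespecify SOFA at 72 h without the neurological item (five items, 0 to 20), analysed as a score, alongside the total score. State beside it how GCS is scored in sedated patients, if the full protocol does not already do so.

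Keep the split at 6 on the total score for comparison with the earlier trauma study. Do not carry the cut of 6 over to the five-item score without a new justification. Interpret an association as perfusion-related organ dysfunction only if it also holds for the five-item score.

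The cost is one additional analysis. The five items are already needed to build the total, so no new assessment is required; the item scores must be kept, not just their sum. The drawback is that the five-item score is less directly comparable with earlier work and leaves out genuine cerebral dysfunction, which is why the total score stays.
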